#### Sustainability of the intervention

The same clinical impact measures will be collected during the "decay" period to determine whether the effects achieved during the "after" period have been sustained.

#### Performance of the Canadian C-Spine Rule

This is a secondary study outcome. The rule will be evaluated during the "after" period at the intervention sites for those cases where physicians have completed the special study requisition and checked off the rule criteria. Rule criteria are:

*Accuracy of the rule, such as sensitivity and specificity for identifying clinically important CSI*. In interpretation of the rule, physician accuracy will be determined by comparing the physicians' notation on the radiography requisition to the "gold standard" interpretation of the rule made by the investigators' steering committee. Attention will be focused on fractures missed or potentially missed by physician misinterpretation.

*Physician comfort and compliance with use of the rule*. On the radiography requisition, physicians will be asked to indicate their comfort in following the rule for that specific patient, using a five-point Likert scale. When physicians choose not to follow the rule, they will be asked to indicate reasons for non-compliance.

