#### Details of planned interventions

Each ED physician group will be asked to discuss and agree to a policy of ordering cervical spine radiography for alert and stable trauma patients according to the Canadian C-Spine Rule. Minor educational initiatives for the ED physicians will include the distribution of manuscripts, pocket cards, and posters, as well as a single one-hour teaching session to review the evidence and clinical application of the Canadian C-Spine Rule. The ED and Radiology departments will collaborate to institute a process-of-care modification with a mandatory "online" reminder of the Canadian C-Spine Rule at the point of requisition for cervical spine radiography. All cervical spine radiography ordered in the ED will require that the ordering physician complete a special paper or computer-based requisition that includes the Canadian C-Spine Rule algorithm criteria. The physician must "check off" the criteria, or the radiology department will not process the request. The physician may override the rule, and order radiography according to his/her clinical judgment, but will be asked to indicate the reason. Those sites that use paper requisitions will implement a new pad of special cervical spine radiography requisitions. Those sites that order radiography by computer will have an on-screen version of the rule made available by software modification.

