### Outcome measures and data collection

#### Measures of clinical impact

The following will be collected at both the intervention and control sites during all three study periods by dedicated study personnel who will review daily patient logs, ED patient records, radiology reports, and inpatient records.

Cervical spine radiography ordering proportions will be the primary study outcome, such as the proportion of eligible blunt trauma patients referred for plain cervical spine radiography during the initial ED visit. Daily patient census logs will be reviewed to identify potential injury patients, and then ED patient records (e.g., ambulance call reports, nursing notes, and physician notes) will be assessed to determine eligibility. Radiology reports and census lists will be used to determine if cervical spine radiography was performed.

*Number of missed CSI, such as number of clinically important CSI not identified during initial ED visit*. We validated the safety of the Canadian C-Spine Rule with detailed follow-up of patients in phase II. In order to significantly reduce the resources required for phase III, we propose not to specifically follow all patients who do not undergo radiography in the ED. Telephone follow-up of patients is very labor intensive and expensive. Rather, we propose to institute a strategy of surveillance to identify the uncommon occurrence of a fracture missed because no radiography was ordered. The more common missed fracture cases due to mis-reading of the radiograph will be identified through the normal radiology department quality assurance processes. ED patient visit logs at each study site will be monitored for 30 days to identify return visits by patients who do not undergo radiography during their ED visit. In addition, we will review the neurosurgery patient logs at all neurosurgical centers that are the traditional referral sites for the study hospitals. In many cases, the regional neurosurgical centers will be our study hospitals. Application of the same surveillance approach, regardless of phase or intervention group, minimizes the likelihood of bias. We recognize that there is a very small risk of not identifying a missed fracture, but feel that this approach is pragmatic and feasible.

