#### Performance of the Canadian C-Spine Rule

Performance of the Canadian C-Spine Rule will be evaluated by the following measures.

Accuracy of the rule: The classification performance of the rule for clinically important CSI will be assessed with 95% CIs for sensitivity, specificity, negative predictive value, and positive predictive value. The "criterion interpretation" of the rule, such as positive or negative for CSI, will be made by the investigators based on the status of the patient for the component variables as documented by the physician.

Physician accuracy in interpretation of the rule will be calculated as the simple agreement between the physicians' notation on the requisition – to the investigators' "criterion interpretation" of the rule.

Physician comfort and compliance with use of the rule will be tabulated in a simple descriptive format.

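### Rule accuracy is to be computed only from completed radiography requisitions, so patients the rule clears without imaging drop out; specificity is biased downward and the sensitivity and NPV are not those of the rule in all eligible patients

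*Protocol article*

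**What the plan says.** Four parts of the protocol article's Methods bear on this.

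- *Outcome measures, Performance of the Canadian C-Spine Rule*: this secondary outcome is evaluated at the intervention sites in the after period, "for those cases where physicians have completed the special study requisition and checked off the rule criteria". Physician accuracy, comfort and compliance are taken from the same form.
- *Details of planned interventions*: "All cervical spine radiography ordered in the ED will require that the ordering physician complete a special paper or computer-based requisition". The reminder sits "at the point of requisition for cervical spine radiography". Overrides are allowed: "The physician may override the rule, and order radiography according to his/her clinical judgment, but will be asked to indicate the reason".
- *Data analysis, Performance of the Canadian C-Spine Rule*: classification performance "will be assessed with 95% CIs for sensitivity, specificity, negative predictive value, and positive predictive value". Rule status is decided by the investigators "based on the status of the patient for the component variables as documented by the physician". No correction for selection and no other data form is mentioned.
- *Outcome measures, Measures of clinical impact*: of patients without imaging, the protocol says "we propose not to specifically follow all patients who do not undergo radiography in the ED". Return visits and neurosurgical logs are monitored instead.

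The rule that every eligible patient is analysed stands under *Data analysis, Measures of clinical impact*. It does not extend to rule performance.

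**The concern.** Entry to the accuracy table depends on the decision to image, and the intervention tries to bring that decision into line with the rule. A patient who is rule-negative and managed accordingly produces no requisition. Rule-negative patients enter only when a physician overrides the rule. This is partial verification bias, and it grows as implementation succeeds: fewer true negatives and false negatives remain in the table.

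Three things are at stake. A valid rule could seem to have lost most of its specificity. NPV would rest only on overridden cases. Physician accuracy and compliance would be observed only among imaged patients, so correct decisions not to image are absent, and so are rule-positive patients who were left without imaging. Readers would naturally set the figures beside those of phases I and II, but they would not be comparable.

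**Working it through.** **Inputs.** From the phase II *Results* and *Summary of findings*: 8,283 patients, of whom 845 were indeterminate (7 with injury); 169 injuries in all; 161 of 162 detected; specificity 45.1%; radiography rate under the rule 55.9%. From *Sample size*: baseline imaging 76%, planned absolute fall 11.4 points, 400 patients per hospital per period. Six intervention sites give 6 × 400 = 2,400 patients in the after period.

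**Reproducing the plan's figure.** Determinate patients: 8,283 − 845 = 7,438. Injured: 169 − 7 = 162. Uninjured: 7,438 − 162 = 7,276. Rule-positive share = (161 + 0.549 × 7,276) / 7,438 = 55.87%, which matches the stated 55.9%. Sensitivity 161/162 = 99.4% also matches.

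**Model.** Let a be the share of rule-positive patients with a requisition and b the share of rule-negative patients with one, with imaging otherwise independent of injury.

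- Imaging rate = 0.5587a + 0.4413b
- Apparent specificity = 0.451b / (0.451b + 0.549a)
- Apparent sensitivity = 0.9938a / (0.9938a + 0.0062b)

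The protocol states neither a nor b. Fixing the imaging rate and assuming a gives b.

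**Planned imaging rate, a = 1.** The rate is 76% − 11.4 = 64.6%, so b = (0.646 − 0.5587) / 0.4413 = 0.198. Apparent specificity = 0.0893 / (0.0893 + 0.549) = 14.0%.

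| Imaging rate | a | b | Apparent specificity | Apparent sensitivity |
|---|---|---|---|---|
| all eligible patients | 1 | 1 | 45.1% | 99.4% |
| 76% | 1 | 0.456 | 27.3% | 99.7% |
| 64.6% | 1 | 0.198 | 14.0% | 99.9% |
| 64.6% | 0.9 | 0.324 | 22.8% | 99.8% |
| 64.6% | 0.8 | 0.451 | 31.7% | 99.7% |
| 60% | 1 | 0.094 | 7.1% | 99.9% |

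**Who is missing.** At 64.6% imaging, 0.354 × 2,400 ≈ 850 patients have no requisition. With a = 1 all of them are rule-negative. The table then holds about 0.4413 × 0.198 × 2,400 ≈ 210 rule-negative patients, all of them overrides, and NPV depends on those alone.

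**Sensitivity.** From 99.4% the largest possible rise is 100 − 99.4 = 0.6 points. As a hypothetical, suppose true sensitivity in practice were 95% and b = 0.2 with a = 1: the table would show 0.95 / (0.95 + 0.05 × 0.2) = 99.0%. At a true 90% it would show 0.90 / (0.90 + 0.10 × 0.2) = 97.8%.

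**PPV.** If having a requisition depends only on rule status, a cancels, and PPV stays at 161 / (161 + 0.549 × 7,276) = 3.9%.

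**Overrides aimed at the injured.** If a = 1, every injured rule-negative patient is imaged and b = 0.2 among the uninjured, sensitivity stays at 99.4%. Apparent specificity is still 14.1%, and NPV moves from 99.97% to 99.85%.

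**The case against.** The other side has substantial points, and several stand.

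- Rule accuracy is a secondary outcome here and was the main business of phase II. The primary comparison uses every eligible patient. This stands.
- A reader might infer that the table will show 100% sensitivity and 0% specificity by construction. That needs full compliance. The protocol allows overrides, reports compliance problems in phase II, and plans an imaging rate (64.6%) above the rule-positive share (55.9%).
- A reader might infer that missed injuries in patients without imaging go unseen. They are missing from this table only. They are a separate outcome, sought by 30-day surveillance at all sites in all periods and compared between arms. An independent board also oversees safety.
- A reader might infer that the whole objective on rule performance is unanswerable. PPV, comfort, override reasons and interpretation agreement remain reportable for requisition cases.
- The effect on sensitivity is small on the documented figures. No passage supports a true value of 95% or 90%. The protocol says physicians override out of concern for the patient's welfare; if that picks out injured patients, sensitivity is hardly inflated.
- The sizes depend on assumed imaging shares. If a is well below 1 and imaging does not fall, little bias remains: a = 0.8 at 76% imaging gives b = 0.709 and apparent specificity 42.1%. The article also does not say whether a requisition begun and then abandoned would be kept; keeping such forms would reduce the bias.

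None of this restores specificity, NPV or a full compliance rate at the imaging rate the trial plans for.

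**Conclusion.** The point holds for the accuracy table. As long as rule-negative patients are imaged less often than rule-positive ones, which is the aim of the intervention, requisition-only specificity is biased downward. At the planned imaging rate, 45.1% would appear as about 14% with all rule-positive patients imaged, and as about 23% or 32% with 90% or 80% imaged. NPV rests on overrides alone, and compliance and physician accuracy describe imaged patients only.

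Under the same condition, applied to the injured, the bias in sensitivity can only be upward and is at most 0.6 points from 99.4%. The concern there is that a real loss in practice could be masked in this table, not that one is expected.

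The figures assume that phase II prevalence, sensitivity and specificity (indeterminate cases excluded) carry over, and that imaging depends on rule status alone. The direction for specificity does not need overrides to be unrelated to injury. The documents do not support a reading that safety goes unmonitored, that the 100% and 0% limits will be reached, or that the primary result is affected.

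**What to change.** In both subsections on the performance of the rule (outcome measures and data analysis), do not report requisition-only sensitivity, specificity and NPV as the rule's accuracy. Report PPV, the override rate, interpretation agreement and comfort, each labelled as among imaged patients. Show the missed injuries found by surveillance at the same sites and in the same period beside them. This is a wording change; its cost is fewer headline accuracy figures.

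Optionally, add a sensitivity analysis in all eligible after-period patients at the intervention sites, about 2,400. Code the rule criteria from the ED records already reviewed for eligibility, class uncodable cases as indeterminate, and give best-case and worst-case bounds. State that patients without imaging have a different reference standard, surveillance, which the protocol concedes can miss a fracture. The cost is extra chart coding and probably many indeterminate cases: range of motion was not evaluated in 10.2% even under prospective assessment in phase II, and the article does not say that the criteria are routinely charted. For these reasons it should support the narrower report and not replace it.

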### Ethical considerations

All the respective research ethics boards have approved the study without the need for informed patient consent at the time of the ED visit. During a particular period in time at a given site, all eligible patients will be managed by the physicians in the same manner, because the unit of study allocation is the hospital, not the patient. As is typical of cluster allocated, matched-pair design studies, individual patients will not be randomized and physicians will order cervical spine radiography in a similar fashion for all patients at their site [48]. Patients will not be subjected to new therapy, invasive procedures, undue risk or discomfort, or use of diagnostic radiography beyond that which would normally be required in the course of patient care. Physicians will be encouraged to use the Canadian C-Spine Rule as a guide for ordering radiography, but will ultimately base their decision on their own judgment as to what is the safest way to manage each individual patient. We note that Canadian physicians are already selective in ordering C-spine radiography, and omitted radiography for 28.3% of cases in phase II. At the same time, we know that the physicians missed some fractures. Patient confidentiality will be maintained throughout the study, and patient names will be removed from all records. The small numbers of patients who are selected for follow-up telephone interviews will have an opportunity to give verbal consent to the ED registered nurse who makes the call. This is consistent with the approach approved by the research ethics boards for follow-up in phases I and II. The safety of the study will be overseen by an independent data monitoring safety board, comprised of a biostatistician, an emergency physician, and a neurosurgeon. This board will have the mandate to terminate the study at any time should there be concerns about adverse patient outcomes.

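### The rule's specificity, sensitivity and NPV are to be estimated only from radiography requisitions, so rule-negative patients who are not imaged drop out and specificity is biased well below its phase II value

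*Protocol article*

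**What the plan says.** The section on performance of the rule, under outcome measures, calls this a secondary outcome. It restricts the evaluation to the after period at the intervention sites, "for those cases where physicians have completed the special study requisition and checked off the rule criteria", and names sensitivity and specificity for clinically important injury as the first item.

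The details of planned interventions show when the form exists: "All cervical spine radiography ordered in the ED will require that the ordering physician complete a special paper or computer-based requisition". A rule-negative patient can still enter, by override: "The physician may override the rule, and order radiography according to his/her clinical judgment, but will be asked to indicate the reason".

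The data analysis section says that accuracy "will be assessed with 95% CIs for sensitivity, specificity, negative predictive value, and positive predictive value". The investigators assign the rule result "based on the status of the patient for the component variables as documented by the physician".

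For patients without a film, the measures of clinical impact state that "we propose not to specifically follow all patients who do not undergo radiography in the ED". In place of full follow-up there is surveillance of 30-day return visits and of neurosurgery logs. The article does not provide for recording the rule components when no film is requested. Its commitment to analyse every eligible patient stands under clinical impact, not under rule performance.

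**The concern.** A 2x2 table for a diagnostic rule needs patients from both sides of the rule. Here the record of the rule result is created by ordering a film, and the implementation strategy exists to make that order rarer when the rule is negative. Selection into the analysis thus depends on the test result, which is partial verification bias.

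Whenever rule-negative patients are imaged less often than rule-positive ones, true negatives are under-counted relative to false positives and measured specificity falls. Rule-negative injuries are under-counted in the same way, so measured sensitivity can only rise. The better physicians comply, the worse the rule's specificity looks. The resulting figures could not be set beside those of phase II, where physicians recorded the rule before radiography and did not use it to decide on films. Accuracy is item (a) of the third specific objective (evaluate performance), so a reader would expect the reported values to describe the rule itself.

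**Working it through.** **Inputs from the protocol article**
- Phase II results: 8,283 patients with 169 injuries; 845 indeterminate cases, seven with injury; specificity 45.1%; film rate under the rule 55.9%. Summary of findings: 161 of 162 injuries identified.
- Sample size: baseline film rate 76%, absolute decrease 11.4%, so the planned rate is 76 − 11.4 = 64.6%; 400 patients per hospital, so 6 × 400 = 2,400 intervention-site patients in the after period.

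**Step 1. Rebuild the phase II table and reproduce a stated figure.**
- Patients: 8,283 − 845 = 7,438. Injured: 169 − 7 = 162. Uninjured: 7,276.
- TP = 161, FN = 1, TN = 0.451 × 7,276 = 3,281, FP = 7,276 − 3,281 = 3,995.
- Rule-positive share = (161 + 3,995)/7,438 = 55.9%, as stated. Rule-negative share = 44.1%.

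**Step 2. Apply the selection.** Let a be the probability of a film in rule-positive patients and c that in rule-negative patients, each taken as unrelated to injury.
- Film rate = 0.559a + 0.441c. Setting it to 0.646 gives c = (0.646 − 0.559a)/0.441.
- Measured specificity = c·TN/(c·TN + a·FP).
- Measured sensitivity = a·TP/(a·TP + c·FN).

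**Step 3. Results at the planned film rate of 64.6%** (a is an assumption, shown as a range)

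| a | c | Measured specificity | Measured sensitivity |
|---|---|---|---|
| 1.00 | 0.198 | 14.0% | 99.9% |
| 0.95 | 0.261 | 18.4% | 99.8% |
| 0.90 | 0.324 | 22.8% | 99.8% |
| 0.85 | 0.388 | 27.3% | 99.7% |
| 0.80 | 0.451 | 31.7% | 99.7% |
| 0.646 | 0.646 | 45.1% | 99.4% |

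First row written out: 0.198 × 3,281 = 649 true negatives; 649/(649 + 3,995) = 14.0%. The last row is the unbiased case, in which film ordering is unrelated to the rule, so the intervention has not made ordering follow it.

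**Step 4. Better compliance.** With a = 1, c = 0.10 gives specificity 7.6% and sensitivity 99.9%. At c = 0 the limits are 0% and 100%.

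**Step 5. Predictive values.** NPV is 3,281/3,282 = 99.97% in the full table and keeps that value for any c above zero if overrides are unrelated to injury. It can move either way if they are related, and is 0/0 at c = 0. PPV uses rule-positive patients only: 161/4,156 = 3.9% whatever c is.

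**Step 6. Records affected.** Un-imaged patients: 2,400 × (1 − 0.646) = 850. With the 25% to 50% relative reduction named under potential benefits, the film rate is 57% to 38%, giving 2,400 × 0.43 = 1,032 to 2,400 × 0.62 = 1,488.

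**The case against.** The strongest reply is that little depends on these figures. The outcome is secondary, and accuracy was the business of phases I and II. The radiography proportion and the other clinical impact outcomes use every eligible patient. That stands, and it limits how serious the point is.

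On sensitivity the reply is largely right. The shift is about half a point at most. At 2.0%, about 48 injuries are expected in 2,400 patients, and 48 × 1/162 = 0.3 of them rule-negative. The exact 95% interval for 48 of 48 is 92.6% to 100%, far wider than the bias. A reader might infer that missed injuries would be hidden. The documents do not support this: such an injury would be missing from the accuracy table, but surveillance is designed to find it and it would be analysed as a missed fracture.

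A reader might also infer that the plan will yield 0% specificity and 100% sensitivity. Those are limits under full compliance. The protocol permits overrides and itself doubts compliance.

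Nor was phase II free of selection. Its 99.4% and 45.1% leave out 845 indeterminate cases (10.2%), because range of motion was not assessed. It is also true that physicians there "omitted radiography for 28.3% of cases in phase II". But that exclusion and those omissions did not come from applying the rule to the ordering decision, and un-imaged patients were followed.

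A form might be started and the request then dropped. The article does not say that such forms are kept, and patients for whom no request was started would still be absent.

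None of this rescues specificity.

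**Conclusion.** The point holds for specificity and should be fixed. As written, the analysis would give about 14% to 32% at the planned film rate against 45.1% in phase II, and less as compliance improves. Sensitivity is biased upward by less than one point, and an injury in an un-imaged rule-negative patient could not count against it. NPV would rest on override cases, has no fixed direction of bias, and cannot be estimated under full compliance.

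The sizes assume that phase II accuracy carries over, that the film rate reaches 64.6%, that 80% to 100% of rule-positive patients are imaged, and that imaging within each rule group is unrelated to injury. The direction for specificity needs only that, among uninjured patients, rule-negatives are imaged less often than rule-positives. More patients would not remove the bias. The primary outcome, the other clinical impact outcomes and the sample size are untouched.

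**What to change.** 1. In both sections on rule performance (outcome measures and data analysis), label the requisition-based results as imaged patients only. From that set report PPV and the number of injuries among rule-negative (override) films. Do not present its sensitivity, specificity or NPV as the rule's accuracy or as comparable with phase II. This costs wording only.

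2. If the rule's accuracy is to be estimated, use all eligible after-period patients at the intervention sites:
   - Abstract the rule components for un-imaged patients from the ED records that study personnel already review.
   - Score the rule before the injury result is attached.
   - Take injuries from radiology reports plus the planned surveillance.
   - Report missing components, notably range of motion, as indeterminate, with a sensitivity analysis.

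The second change adds a few fields for about 850 records at the planned effect, and for about 1,030 to 1,490 if the reduction is 25% to 50%. Its downside is missing chart items and less complete outcome ascertainment in un-imaged patients. Phase II physicians, recording prospectively, still left range of motion unassessed in 10.2%, so routine charts may do no better. Weighting imaged patients by their probability of imaging is not a way round the abstraction: that probability depends on rule status, which is unrecorded in un-imaged patients, and no weight exists if no rule-negative patient is imaged.
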